### Randomization

A randomization sequence was generated using SAS 9.4 (SAS Institute Inc., Cary, NC, USA). An independent person ([name]) who is not involved in observation or assessment of the patients possesses the computer-generated randomization sequence. The researchers are blinded to the randomization sequence. The randomization procedure will be conducted by research assistants using an online computerized randomization system (https://sci.njpdkj.com/pdsci/). Eligible participants will be randomly assigned to either the TCM group or azathioprine group.

### Interventions

#### Basic treatment

All eligible steroid-dependent patients will continue their initial steroid and 5-aminosalicylic therapy. Withdrawal of steroids occurs along with clinical remission. If there is clinical remission, a taper dose will be initiated with 5 mg taper weekly until a 20 mg daily dose is reached. Then tapering should proceed by 2.5 mg per week [11].

#### Chinese herbal medicine granules

Patients in the TCM group will be treated with basic treatment plus granules. The granules include *Radix Astragali* (Huangqi) 20 g, *Rhizoma Atractylodis Macrocephalae* (Baizhu) 10 g, *Semen Coicis* (Yiyiren) 20 g, *Rhizoma Dioscoreae* (Shanyao) 20 g, *Rhizoma Coptidis* (Huanglian) 6 g, *Radix Scutellariae* (Huangqin) 10 g, *Radix Pulsatillae* (Baitouweng) 10 g, *Rhizoma Smilacis Glabrae* (Tufuling) 15 g, *Radix Angelicae Dahuricae* (Baizhi) 12 g, *Radix Paeoniae Alba* (Baishao) 20 g, *Pericarpium Citri Reticulatae* (Chenpi) 12 g, *Radix Saposhnikoviae* (Fangfeng) 12 g, *Radix Aucklandiae* (Muxiang) 6 g, *Radix Sanguisorbae* (Diyu) 10 g, *Radix Arnebiae* (Zicao) 10 g, *Radix et Rhizoma Rubiae* (Qiancao) 20 g, *Fructus Alpiniae Oxyphyllae* (Yizhi) 10 g, *Rhizoma Zingiberis Preparata* (Paojiang) 6 g, and *Radix et Rhizoma Glycyrrhizae* (Gancao) 6 g. All ingredients are manufactured as a Chinese herbal granule with a weight 27.5 g (Jiangyin Tianjiang Pharmaceutical Co., Ltd, Jiangyin, China). Patients will take one Chinese herbal medicine granule per day. The course of treatment is 24 weeks unless there is a loss of follow-up.

#### Azathioprine

The control group will take basic treatment plus azathioprine. Azathioprine treatment can be initiated at a dosage of 1 mg/kg per day [12, 13]. The course of treatment will be in accordance with the TCM group.

### Outcome measures

#### Primary outcome measure

The primary outcome measure of this study is the steroid-free remission rate in patients with steroid-dependent ulcerative colitis. Remission is defined as a Mayo disease activity index score of 0–2, with no individual subscore exceeding 1 [14]. The withdrawal time of steroids will also be recorded. The outcome measure will be evaluated at the end of 24 weeks. If there is no statistical significance between the steroid-free remission rate of the TCM group and the azathioprine group, then the mean withdrawal time from steroids will be compared.

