### Sample size

The remission rate for ulcerative colitis by azathioprine ranges from 59.1% to 87% [9, 10], and the average rate is about 73%. This is a noninferiority trial. For a two-sided significance level of 0.05 and power of 80% (*α* = 0.05, *β* = 0.2, *δ* = 0.15), the sample size is calculated using the formula:$$ n=12.365\times P\left(1-P\right)/{\delta}^2 $$

Considering a 10% loss to follow-up, the sample size is 120 cases (*n* = 60 in each group).

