### Data management and statistical analysis

Data recorded in printed case report forms are kept in locked cabinets. Data will be double-entered on electronic case report forms by two persons. Frequency, median, and mean ± standard deviation of the steroid-free remission rate and the mean withdrawal time of steroids will be used for descriptive statistics. Student’s *t* test and analysis of variance will be employed using continuous variables with a normal distribution. The Mann–Whitney *U* test and Kruskal–Wallis test will be used for continuous variables with abnormal distributions, such as health-related quality of life and inflammation markers. A chi-square test or Fisher’s exact test will be used for categorical variables, including the efficacy of endoscopic response and the degree of mucosal healing. Results will be analyzed as per intention-to-treat. All data will be analyzed by an independent statistician using SAS 9.4. For all analyses, *P* < 0.05 is considered statistically significant.

To summarize the present study protocol, please see Additional file 1 for an overview of enrollment, interventions and assessments, and Additional file 2 for an overview of the Standard Protocol Items: Recommendations for Interventional Trials (SPIRIT) checklist.

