
Chinese herbal medicine is a type of complementary and alternative medicine, and is often used in patients with inflammatory bowel disease [8], especially in China. Dai *et al.* [23] analyzed 247 patients with ulcerative colitis. The Sutherland Disease Activity Index scores for patients treated with TCM and those treated with integrated TCM and Western medicine were significantly lower for both groups after treatment (*P* < 0.01). Sugimoto *et al.* used the Chinese herbal medicine Qing-Dai to treat 20 patients with moderate ulcerative colitis. The rates of clinical response, clinical remission, and mucosal healing were 72%, 33%, and 61% at week 8, respectively [24]. Qing-Dai stimulates mucosal type 3 innate lymphoid cells to generate interleukin-22, which induces antimicrobial peptide and tight junction production, suggesting a therapeutic mechanism for mucosal healing [25]. Our study using Chinese herbal medicine plus 5-aminosalicylic in patients with steroid-dependent ulcerative colitis aims to observe improvements in the primary outcome of steroid-free remission rate, and the secondary outcomes of health-related quality of life, endoscopic response, mucosal healing, and inflammation indicators. We expect that the steroid-free remission rate of the TCM group will be improved over that of the azathioprine group. The mean withdrawal time of steroids in the TCM groups should be less than that of the azathioprine group, which would reduce the risks of steroid therapy. We anticipate that the results will show that Chinese herbal medicine is effective for patients with steroid-dependent ulcerative colitis.

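### Steroid withdrawal time is compared only if the primary comparison is not significant: an inverted gate that can raise the false-positive rate to as much as 9.75% and does not fit a noninferiority design

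*Protocol article*

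**What the plan says.** The protocol article names steroid-free remission at 24 weeks as the primary outcome. The same section adds that withdrawal time will be recorded and sets a condition for analysing it: "If there is no statistical significance between the steroid-free remission rate of the TCM group and the azathioprine group, then" the groups are compared on mean withdrawal time.

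Four other places bear on this rule:

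- Data management and statistical analysis sets one threshold throughout: "For all analyses, *P* < 0.05 is considered statistically significant".
- Secondary outcome measures lists quality of life, endoscopic response, mucosal healing and inflammation indicators. Withdrawal time is not in that list.
- Sample size declares the design: "This is a noninferiority trial", with a margin of 0.15.
- Discussion states the expected direction: "The mean withdrawal time of steroids in the TCM groups should be less than that of the azathioprine group". It also expects a better remission rate with TCM.

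**The concern.** In a valid fixed sequence, a later outcome is tested after the earlier one has succeeded, so the sequence as a whole spends the significance level once. Here failure opens the second test, and that test is run at the full 0.05. If either result may be claimed, the combined false-positive rate exceeds 0.05.

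The rule also uses the language of a difference test in a trial declared to be noninferiority. There are two ways to read it, and neither is sound:

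- If it means that noninferiority was not shown, the trial gets a second chance after failing its main objective.
- If it means that no difference was detected, a non-significant result is taken as evidence that the rates are similar. With 60 patients per group it is not.

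At stake is a favourable withdrawal-time result being put forward at the level of the primary outcome when noninferiority on remission has not been established.

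**Working it through.** **Inputs.** From Sample size: "For a two-sided significance level of 0.05 and power of 80" percent, margin 0.15, azathioprine remission rate 0.73 ("the average rate is about 73" percent), 10% loss, 60 per group (so 54 after loss). From the statistical section: 0.05 for each test. The correlation between the two tests is not given, so a range is assumed.

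**The plan's own figure.** The article states no overall false-positive rate, only 0.05 per test. Its one design calculation reproduces as a total: 12.365 × 0.73 × 0.27 / 0.15² = 108.3, and 108.3 / 0.9 = 120.4, given as 120. The constant 12.365 equals 2(1.645 + 0.842)², which is a one-sided 0.05, per-group constant. That is a separate matter, but it affects how often the gate opens (last step).

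**False-positive rate of the rule.** Assume no true difference on either outcome and two-sided 0.05 difference tests. With independent tests:

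0.05 + 0.95 × 0.05 = 0.0975.

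With correlated tests the rate is one minus the bivariate normal probability that both statistics lie within ±1.96. The first significant result closes the sequence, so by symmetry half of these errors favour TCM. With independent tests that half is 0.025 + 0.95 × 0.025 = 0.049.

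| Correlation | At least one significant | Favouring TCM |
|---|---|---|
| 0 | 9.75% | 4.9% |
| 0.3 | 9.5% | 4.8% |
| 0.5 | 9.1% | 4.5% |
| 0.7 | 8.4% | 4.2% |
| 0.9 | 7.0% | 3.5% |
| 0.95 | 6.5% | 3.2% |

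The reference values are 5% and 2.5%.

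**Simulation.** This used 60 per group, 73% remission in both arms and 20,000 trials. It assumed withdrawal times uniform over 6 to 22 weeks, with non-remitters counted as not withdrawn. The remission test alone rejected in 5.3%. The full rule rejected in 10.2% if times are compared only among those who withdrew, and in 8.2% if the others are set to 24 weeks. The 10.2% lies slightly above 9.75% because the chi-square test itself runs at 5.3% here and because of simulation error.

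**How often the gate opens.** The answer depends on which reading is meant.

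- *Gate is a difference test.* With TCM truly 15 points worse (58% against 73%), exact enumeration gives a non-significant chi-square in 58.8% of trials with 60 per group and 61.8% with 54.
- *Gate is failed noninferiority, same truth.* By definition of the test level it opens in about 95% (one-sided 0.05) or 97.5% (one-sided 0.025).
- *Gate is failed noninferiority, both rates 73%.* Power is Φ(0.15 / √(2 × 0.73 × 0.27 / m) − z). With m = 60 and z = 1.645 this is Φ(0.15/0.0811 − 1.645) = 58%, and with m = 54 it is 54%. At one-sided 0.025 the figures are 46% and 42%. The gate therefore opens in about 42% to 58% of trials even when the treatments are equally effective.

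Under each of these scenarios the second test is a common path.

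**The case against.** The strongest defence is that the comparison is only supportive. Steroid-free remission is consistently named as the primary outcome, withdrawal time is described as something also recorded, and the abstract presents the findings as a basis for later confirmatory work. On a natural reading the authors mean that, if remission looks similar, they will ask whether TCM allows earlier withdrawal. An analysis plan that is not shown may also contain a multiplicity rule.

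Part of this stands. A reader might infer that withdrawal time is a fallback primary outcome whose significance would make the trial positive. No section says so, and the point does not rest on it. Nor can the absence of an adjustment be charged, since that may be set out elsewhere. What can be criticised is the gate that the article does fix. It sits under the primary outcome heading, concerns an outcome missing from the secondary list, and comes with a favourable expectation in the Discussion. The supportive reading has its own fault, because it treats non-significance as similarity.

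A reader might also infer that the error rate simply doubles. That holds only near independence. Steroid-free remission requires withdrawal, so correlation is plausible and the inflation smaller. In addition, 9.75% counts errors in both directions, while the harm described here is a false claim for TCM, which stays below 5%. Finally, the 59% to 62% gate-opening figure applies only if the gate is a difference test.

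**Conclusion.** The concern holds in limited form. The protocol article fixes a rule that opens a second 0.05-level test after the first has failed, and the wording of that rule has no defined meaning in a noninferiority trial. If both tests are two-sided difference tests at 0.05 and either may be claimed, the chance of at least one false-positive result is at most 9.75%, falling to 7.0% at correlation 0.9. For errors favouring TCM alone it rises from 2.5% to at most about 4.9%. It exceeds the nominal level at every correlation examined, so the defect does not depend on the exact value, which the document does not supply. These figures assume tests of exact size and no true difference on either outcome. The text invites a claim based on withdrawal time but does not state one.

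**What to change.** 1. Delete the conditional sentence under Primary outcome measure.
2. State that the primary analysis is the noninferiority comparison of week-24 steroid-free remission against the 0.15 margin, and give its significance level and sidedness.
3. List withdrawal time under Secondary outcome measures and report it whatever the primary result.
4. If withdrawal time is to support a claim, test it only after noninferiority on remission has been shown, at the same level. With this order the chance of any false claim stays at the level of the primary test, 5% if that is 0.05, against up to 9.75% now.

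The change moves and rewords one sentence and adds one. It needs no new data and can be made before analysis. The downside is that the fallback claim is lost: if noninferiority is not shown, a withdrawal-time difference can be described but not claimed.

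### The fallback comparison of mean steroid withdrawal time has no rule for patients still on steroids at week 24, and a mean over observed times can favour the worse arm

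*Protocol article*

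**What the plan says.** All references are to the protocol article.

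- **Primary outcome measure.** The primary outcome is the steroid-free remission rate, with this timing: "The outcome measure will be evaluated at the end of 24 weeks". Withdrawal time is recorded as well. A fallback applies when the two arms' rates are not significantly different: "then the mean withdrawal time from steroids will be compared".
- **Basic treatment.** Stopping steroids depends on response: "Withdrawal of steroids occurs along with clinical remission". On remission, the dose comes down by 5 mg each week as far as 20 mg a day; for the remainder the article says: "Then tapering should proceed by 2.5 mg per week".
- **Data management and statistical analysis.** The steroid-free remission rate and "the mean withdrawal time of steroids will be used for descriptive statistics", as frequency, median and mean with standard deviation. The tests named are the t test and analysis of variance, Mann–Whitney and Kruskal–Wallis, and chi-square or Fisher. No time-to-event method appears. The section also states: "Results will be analyzed as per intention-to-treat".
- **Discussion.** The authors expect a shorter mean withdrawal time with traditional Chinese medicine (TCM) than with azathioprine, and read it as lowering the risks of steroid therapy.

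**The concern.** Withdrawal time is an event time. A patient who has not remitted, or who remitted too late to complete the taper, has no value at week 24. The article nevertheless fixes the comparison as one of means and names only tests that need a complete value for each patient analysed.

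If the mean is taken over the times that were observed, three problems follow:

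1. The patients compared are selected by a post-randomization outcome that treatment itself affects, so randomization no longer protects the comparison.
2. Times are truncated at week 24. An arm that brings additional patients off steroids late in follow-up lengthens its own mean and is penalised for those successes.
3. The result cannot be reconciled with the intention-to-treat statement.

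The Discussion already attaches a benefit to a shorter mean, so the statistic would feed an interpretation that the authors have in view. It would do so just when the primary comparison has not separated the arms.

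**Working it through.** The article gives no planning figure for withdrawal time, so there is none to reproduce. The check takes the document's rates and taper rule, then an assumed example.

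**1. How many patients would have no withdrawal time?**
Inputs: 60 per group, and azathioprine remission rates of 59.1% to 87% averaging about 73% (Sample size). Number without a time = 60 × (1 − rate).

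| Rate | Calculation | Per arm | Share |
|---|---|---|---|
| 59.1% | 60 × 0.409 = 24.5 | about 25 | 41% |
| 73% | 60 × 0.27 = 16.2 | about 16 | 27% |
| 87% | 60 × 0.13 = 7.8 | about 8 | 13% |

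This is an approximate proxy. The Discussion describes the 87% as a remission rate, not a steroid-free one, and failing steroid-free remission is not the same as never stopping steroids.

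**2. Does the taper itself produce censoring by week 24?**
Weeks from dose D (mg/day) to zero under the written taper = max(D − 20, 0)/5 + min(D, 20)/2.5. Latest start that can finish in follow-up = 24 − that number.

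| D | Weeks to zero | Latest start (week) |
|---|---|---|
| 20 mg | 0 + 8 = 8 | 16 |
| 30 mg | 2 + 8 = 10 | 14 |
| 40 mg | 4 + 8 = 12 | 12 |
| 60 mg | 8 + 8 = 16 | 8 |

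The article gives no starting doses, so the doses in this table are assumptions. A patient at 20 mg who begins the taper after week 16 is in remission but cannot have a withdrawal time by week 24.

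**3. Can the comparison reverse while the fallback applies?**
Assumed data, 60 per arm. Arm A: 36 stop, mean week 13. Arm B: the same 36, plus 8 more who stop at mean week 22. B is better, since it has everything A has and 8 further successes. The proportion stopping stands in for steroid-free remission.

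- Gate: 36/60 against 44/60. The pooled proportion is 80/120 = 0.667 and the difference 0.133. SE = √(0.667 × 0.333 × 2/60) = 0.0861, so z = 1.55 and chi-square = 2.40 (uncorrected), p = 0.12. Fisher's exact test gives p = 0.17. Neither is significant, so the fallback is triggered.
- Mean over those who stopped: A = 13.0 weeks; B = (36 × 13 + 8 × 22)/44 = 644/44 = 14.6 weeks. This favours A, the worse arm.
- Restricted mean time on steroids to week 24, all 60: A = (36 × 13 + 24 × 24)/60 = 1044/60 = 17.4 weeks; B = (36 × 13 + 8 × 22 + 16 × 24)/60 = 1028/60 = 17.1 weeks. This favours B.

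**4. How often could that happen with the gate applied?**
Simulation, 60 per arm: chi-square on the proportion stopping, then a t test on observed times only if chi-square is non-significant. All event-time inputs are assumed.

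| Assumed pattern | Gate open | Of those, t test significantly favours the worse arm |
|---|---|---|
| 60% stop early in both arms (mean about 13 weeks, SD 3); better arm has a further 13% stopping in weeks 20–24 | about 68% | about 47% |
| Exponential remission time (mean 8 weeks) plus tapers of 4, 8, 12 or 16 weeks; worse arm fails in 30% of long-taper patients (80% vs 69% stop) | about 73% | about 6 to 7% |
| Same taper mix; remission only slower in the worse arm (mean 13 vs 10 weeks) | about 82% | about 1% |
| Identical arms, 60% stop early | about 95% | about 2% (one direction, nominal) |

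The frequency runs from negligible to nearly half, depending on who stops late.

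**The case against.** **The text never restricts the comparison to patients who stopped.** It says that times are recorded and their mean compared, next to an intention-to-treat statement. Non-stoppers might be counted to week 24, or ranked last in a Mann–Whitney test, and either would remove the selection. A condensed article may leave that rule to a fuller plan. This stands in part: a reader might infer that the protocol commits to an analysis of withdrawers only and so contradicts intention-to-treat outright, and the article does not support that. It does fix a comparison of means, with tests for complete data, on an outcome that some patients will not have. That choice is visible here and is not merely missing detail.

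**The comparison is gated.** Withdrawal times are compared only when remission rates do not differ significantly. Where one arm takes many fewer patients off steroids, the primary test will usually show it and the fallback will not run. This stands, and it rules out gauging the harm from scenarios with large gaps in the proportion stopping. The worked example therefore keeps the gate open. The descriptive summary of mean withdrawal time carries no gate.

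**Reversal needs a particular pattern.** This also stands. Plain slowing of remission hardly ever produces a significant reversal. A reader might infer that the planned analysis will favour the worse arm; the documents do not support that.

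**The Discussion voices an expectation, not an analysis plan.** It also expects a higher steroid-free remission rate with TCM. It would overstate the text to say that a shorter mean is to be presented as a benefit whatever the primary result. It does show how a shorter mean would be read.

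**Conclusion.** The concern holds in this form: the fallback compares means of a time that patients still on steroids at week 24 do not have, no rule covers those patients, and the named tests do not accommodate censoring. By the article's remission rates, roughly 13% to 41% of an arm could be affected, as an approximate proxy. A mean over observed times would be selected on outcome, would ignore the week-24 cut-off, and could not be squared with intention-to-treat. The assumed example shows that it can favour the worse arm with the gate open (13.0 against 14.6 weeks, when 17.4 against 17.1 weeks is the all-patient result).

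Confidence is high that a rule is missing and the method unsuitable. How often the direction would reverse cannot be known from the document. The primary endpoint is untouched, so this should be corrected but does not undermine the trial.

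**What to change.** Replace the comparison of means, in both the primary outcome and analysis sections, with an analysis of time from randomization to steroid withdrawal in all randomized patients:

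- Use Kaplan-Meier curves with a log-rank test, or the difference in restricted mean time on steroids to week 24. Name one of them in advance.
- Censor patients not withdrawn by week 24 at that point, or for the restricted mean count them to week 24.
- In the analysis, count patients who leave for treatment failure or have colectomy as not having achieved withdrawal, rather than censoring them when they leave. State how a restart of steroids after withdrawal is classified.
- Any mean or median among those who stopped should be descriptive only, shown beside the number who stopped in each arm, with no test and no claim of benefit.

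The cost is analysis wording only, because withdrawal time is already recorded. The wording should be settled before outcome data are compared between arms.

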#### Secondary outcome measures

The key secondary aim is to investigate the effect of Chinese herbal medicine granules on health-related quality of life in steroid-dependent patients compared with azathioprine, as measured by the inflammatory bowel disease questionnaire. Other secondary outcome measures include the efficacy of endoscopic response, which is defined as a decrease from baseline in a Mayo disease activity index endoscopy subscore by at least 1 [14]. The degree of mucosal healing is defined as a Mayo disease activity index endoscopy subscore of 0 or 1 [15]. Improvements in inflammation indicators include fecal calprotectin, C reactive protein, and erythrocyte sedimentation rate.

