## Background

Ulcerative colitis is a form of inflammatory bowel disease characterized by a chronic relapsing clinical course. Intermittent rectal bleeding, diarrhea, and abdominal pain are often symptoms of ulcerative colitis. 5-Aminosalicylic acid is usually used in mild cases of ulcerative colitis. Steroids are another effective therapy for inducing remission in patients with moderate and severely active ulcerative colitis. Approximately 20–34% of patients with ulcerative colitis have chronic active disease requiring several courses of steroids to achieve remission [1, 2]. Many patients initially benefit from steroid treatment but relapse shortly after treatment cessation or after dose reduction. Up to 20% of patients with ulcerative colitis become steroid dependent [3]. The European Crohn’s and Colitis Organisation guidelines define “steroid-dependent” patients as those who are unable to reduce steroids below the equivalent of prednisolone 10 mg/day within 3 months of starting steroid use, without recurrent active disease, or who have a relapse within 3 months of stopping steroid use [4]. The risks of long-term steroid therapy include osteoporosis, pathological fractures, cataracts, metabolic changes, psychological disturbances, and infection. Moreover, steroids have not been shown to be effective for the maintenance of remission.

The American College of Gastroenterology and European Crohn’s and Colitis Organisation guidelines recommend that patients with steroid-dependent disease should be treated with azathioprine or 6-mercaptopurine [5, 6]. Azathioprine is significantly more effective than 5-aminosalicylic acid at achieving clinical and endoscopic remission in the treatment of steroid-dependent ulcerative colitis. In a single-center retrospective cohort study, 64 Asian patients with steroid-dependent inflammatory bowel disease were assessed, and 61% of patients were able to maintain clinical remission after 5 years of azathioprine therapy [7]. Toxicity induced by azathioprine and 6-mercaptopurine in patients with inflammatory bowel disease includes bone marrow suppression, drug-induced hepatitis, pancreatitis, and infection.

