### Eligibility criteria

Participants will be considered for enrollment if they: range in age from 18 to 65 years; have a confirmed diagnosis of steroid-dependent ulcerative colitis; agree to participate in this clinical trial; and sign the informed consent form.

Patients will be excluded from the study if they: experience complications such as intestinal obstruction, intestinal perforation, toxic megacolon, or colorectal cancer; are pregnant, breast-feeding, or preparing for pregnancy; have an alanine aminotransferase level above the twice upper limit of normal; have a serum creatinine level above the upper limit of normal; have a platelet value of less than 50 × 10^9^/l; have a leukocyte count of less than 3.0 × 10^9^/l; have a known history of alcohol or drug abuse; or are enrolled in other clinical trials.

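### Entry does not require active disease, so a patient entering at Mayo endoscopy subscore 0 can never count as an endoscopic responder

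*Protocol article*

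**What the plan says.** All of the following is in the protocol article.

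- **Entry.** Under Eligibility criteria the only disease requirement is that patients "have a confirmed diagnosis of steroid-dependent ulcerative colitis". The exclusions cover patients who "experience complications such as intestinal obstruction, intestinal perforation, toxic megacolon, or colorectal cancer", then pregnancy, laboratory limits, substance abuse and other trials. None concerns inactive disease.
- **Steroid dependence.** The Background cites a guideline definition based on history. One branch is being "unable to reduce steroids below the equivalent of prednisolone 10 mg/day within 3 months of starting steroid use, without recurrent active disease"; the other is relapse within 3 months of stopping. The Discussion also describes dependence by past course.
- **Treatment at entry.** Basic treatment states: "All eligible steroid-dependent patients will continue their initial steroid and 5-aminosalicylic therapy". The taper depends on remission: "If there is clinical remission, a taper dose will be initiated with 5 mg taper weekly until a 20 mg daily dose is reached".
- **Remission.** Primary outcome measure: "Remission is defined as a Mayo disease activity index score of 0–2, with no individual subscore exceeding 1".
- **Endoscopic outcomes.** Secondary outcome measures describes response as an outcome "which is defined as a decrease from baseline in a Mayo disease activity index endoscopy subscore by at least 1". For healing it says: "The degree of mucosal healing is defined as a Mayo disease activity index endoscopy subscore of 0 or 1".
- **Analysis.** Data management and statistical analysis assigns both outcomes to a chi-square or Fisher's exact test, states intention-to-treat as the general rule, and prints no restriction or adjustment by baseline subscore.

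**The concern.** A change outcome needs room to change. Steroid dependence can be met by a patient whose disease is quiet on the current dose and returns when the dose is cut. If that patient's endoscopy is normal at entry, the response definition cannot be met. The patient adds a certain failure to whichever arm they join, and that failure says nothing about treatment.

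At stake is the reading of a secondary outcome. The reported response rate would be too low as a description of patients who had something to improve, and the difference between arms would be too small. The Sample size section calls this a noninferiority trial, so a difference reduced by the definition could be mistaken for similarity of the treatments.

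Mucosal healing raises a related question of interpretation. A patient entering at 0 or 1 already meets its criterion, so the week-24 rate combines healing achieved on treatment with healing kept during steroid withdrawal.

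**Working it through.** The article gives no rate, power or sample size for either endoscopic outcome, so there is no figure to reproduce. The check is first logical, then illustrative.

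**1. Can a patient enter at subscore 0?** Nothing in the inclusion or exclusion list prevents it. Under the article's own remission definition no subscore exceeds 1, so anyone in remission on steroids at entry has an endoscopy subscore of 0 or 1.

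**2. Each baseline subscore against the two definitions.**

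| Baseline subscore | Can fall by at least 1? | Meets the healing criterion at entry? |
|---|---|---|
| 0 | No | Yes |
| 1 | Yes, by reaching 0 | Yes |
| 2 | Yes | No |
| 3 | Yes | No |

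Only baseline 0 rules out response.

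**3. Effect on the response comparison.** Let f be the share entering at 0, equal in both arms, and p1 and p2 the response rates among the rest. The measured rates are (1 − f)p1 and (1 − f)p2, the ceiling is 1 − f, and the measured difference is (1 − f)(p1 − p2). Assume p1 = 70% and p2 = 50%, neither of which is in the article:

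| f (assumed) | Ceiling | Measured rates | Difference |
|---|---|---|---|
| 10% | 90% | 63% v 45% | 18 points |
| 20% | 80% | 56% v 40% | 16 points |
| 30% | 70% | 49% v 35% | 14 points |
| 40% | 60% | 42% v 30% | 12 points |

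**4. Does restriction help once patients are lost from the denominator?** Take f = 30%, the article's 60 per arm, and a two-sided 5% test (normal approximation, unpooled standard error).

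- All 60 per arm, 49% v 35%: SE = √[(0.49×0.51 + 0.35×0.65)/60] = 0.089; 0.14/0.089 = 1.57; power = Φ(1.57 − 1.96), about 35%.
- Baseline at least 1, 0.7 × 60 = 42 per arm, 70% v 50%: SE = √[(0.70×0.30 + 0.50×0.50)/42] = 0.105; 0.20/0.105 = 1.91; power = Φ(1.91 − 1.96), about 48%.

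Restriction gains power despite the smaller number, because the patients removed could only be failures. Power is low either way.

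**5. Is healing diluted in the same way?** Not necessarily. Assume 30% enter at 0-1, and 70% v 50% of the others heal.

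- If 90% of those entering at 0-1 stay there in both arms: 0.7×70 + 0.3×90 = 76% v 0.7×50 + 0.3×90 = 62%, a 14-point difference.
- If 80% v 60% stay there: 0.7×70 + 0.3×80 = 73% v 0.7×50 + 0.3×60 = 53%, a 20-point difference with no dilution.

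The result depends on whether treatment affects maintenance, which the trial is designed to find out.

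**The case against.** The strongest reply is that the affected group may be small. The eligibility list does not itself adopt the Background definition. The Discussion describes patients who relapse and need steroids again. The taper begins only on remission and first steps down to 20 mg, which suggests that many entrants are expected to be active. This stands as a limit on size: no share of quiet entrants can be derived from the article. It does not remove the fault, because nothing makes activity a condition of entry.

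A second reply is that this is a condensed article, and a full protocol or analysis plan could set the denominator. It could. But the article prints a complete response definition beside a detailed entry list, and the two together produce the fault.

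Stronger readings that a reader might infer, and why they fail:

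- *The trial demands inactive disease.* It does not; it is silent on activity.
- *Every patient at 0 or 1 is barred from response.* A patient at 1 responds by reaching 0.
- *Patients healed at entry are free successes on mucosal healing.* These patients are selected because disease returns as steroids fall, so staying at 0-1 through withdrawal is a legitimate result. Dilution of the healing difference is not a general consequence (step 5).
- *Chance imbalance in baseline subscore biases the results.* It is ordinary randomisation variance, already allowed for in the chi-square or Fisher test.
- *The two outcomes contradict each other.* One measures change and the other status, so one patient may fail the first and meet the second.

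**Conclusion.** The point holds for endoscopic response. As printed, a patient entering at subscore 0 is a non-responder by definition. The response rate is capped at 1 − f and the difference is multiplied by 1 − f. That much is certain in logic. Its size is unknown: a 20-point difference becomes 18 to 12 points if f is 10% to 40%, assuming equal shares in both arms. At f = 30% and assumed rates of 70% v 50%, restriction raises power from about 35% to about 48%.

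For mucosal healing the documents support only a request for clearer reporting. The definition is sound as a week-24 status outcome, but its rate mixes two kinds of result that should be shown apart.

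The primary outcome analysis is not in question here. The article names quality of life as the key secondary aim and lists the endoscopic outcomes after it. This is an inexpensive improvement, not a threat to the trial.

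**What to change.** **Endoscopic response.** In Secondary outcome measures and in Data management and statistical analysis, define it among patients with a baseline Mayo endoscopy subscore of at least 1. The subset depends only on a baseline value, so the comparison stays randomised provided that the baseline endoscopy precedes randomisation. State this, and report the number excluded in each arm.

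**Mucosal healing.** Keep subscore 0 or 1 at week 24 in all randomised patients. Stratify the comparison by baseline subscore (0-1 v 2-3), for example with a Cochran–Mantel–Haenszel test. Report new healing (baseline 2-3) and maintained healing (baseline 0-1) separately by arm.

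**Cost.** The change rewords two secondary outcomes and adds one stratified test. No new data are needed, since response is already defined from baseline. The response denominator falls by the share at subscore 0: from 60 per arm to between 54 and 36 for shares of 10% to 40%. Because the trial is open-label, the change should be fixed and dated before outcomes are examined by arm.
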